## **b. Data Fields to be collected**

Below (Table 2) we summarize the existing data required for the evaluation. A detailed list of data fields follows this summary.

**Table 2. Data required for the evaluation**

| **Objective** | **Data that must be fully captured by routine data collection systems and procedures** |
| --- | --- |
| Fast track ART initiation counseling (Objective 1) | Scheduled and actual visit date information, CD4 counts and dates when results are received, date at which ART eligibility is determined, date of first ARV dispensing, viral loads. |
| Enhanced adherence counseling (Objective 2) | Scheduled and actual visit information, date of eligibility for enhanced adherence counseling, dates of delivery of counseling, viral loads. |
| Adherence clubs (Objective 3) | Club membership, scheduled and actual visit/club participation information, date of eligibility, dates of all medication pick ups, viral loads. |
| Decentralized medication delivery (Objective 4) | Scheduled and actual visit information, date of eligibility, dates of all medication pick ups, viral loads. |
| Early tracing (Objective 5) | Scheduled and actual visit information, date of eligibility, numbers and types of tracing attempts made, results of tracing, viral loads. |
| Overall impact (Objective 6) | Aggregate figures of total numbers of patients presenting and eligible for each intervention (aggregate at clinic level).*  (*Note: as these data do not pertain to individual human subjects, they are not included in the list of fields below.) |
| Cost estimates of interventions (Objective 7) | Unit costs of all resources utilized to implement the interventions.* (*Note: as these data do not pertain to individual human subjects, they are not included in the list of fields below.) |
| TB, diabetes and hypertension (Objective 8) | Records for all patients recently screened for these conditions, all laboratory tests and clinical investigations done relating to these conditions (including blood pressure, HbA1c test and TB test results), scheduled and actual visit information, dates of eligibility, dates of all medication pickups, and outcome data. |

The specific data fields available and required for each cohort will vary slightly (e.g. viral loads will not be available for patients newly initiating treatment under Objective 1). In general, however, we will collect a common set of variables for all patients enrolled Cohorts 1-5, and a different set of variables for patients enrolled in Cohort 8, as listed below.

*Objectives 1-6, all cohorts:*

- Electronic medical record system number (e.g. Tier.Net record number)*
- Clinic file, register, and card numbers (assigned by the clinic)*
- National ID number*
- Name*
- Date of birth*
- Weight and height or BMI
- Sex
- Age in years
- Marital status if recorded
- Employment status if recorded
- Education level if recorded
- Smoking and alcohol use if recorded

*To be used to link electronic and paper-based records pertaining to individual patients. Many clinics use name or initials and date of birth to create a clinic record number.

*Objectives 1-5, HIV cohorts:*

- Date of positive HIV test (if available)
- Dates of all clinic visits (including pre-ART and after ART initiation)
- Primary purpose of all clinic visits (e.g. HIV test, CD4 count, counselling, ARV dispensing, ART monitoring, etc.)
- Dates of next scheduled clinic visits (dates patients are expected to return to clinic)
- Date treatment eligibility determined, if reported
- Date and result of CD4 count indicating treatment eligibility (baseline)
- WHO stage and clinical conditions
- Date and result of TB symptom screen
- Date, type, and result of TB test
- Date TB treatment initiated, if relevant*
- Date and result of cryptococcal meningitis test
- Date cryptococcal meningitis treatment initiated, if relevant*
- Date ART initiated (first dose of medications dispensed)
- First-line regimen prescribed
- Any changes to first line regimens and dates of changes
- Dates and results of all viral load tests
- Dates and results of all other laboratory investigations
- All completed fields in Adherence Plan, if entry into an electronic database is feasible (attached)
- Dates of eligibility for receiving interventions
- Dates of participation in intervention activities or receipt of intervention services (e.g. Adherence Club visits, tracing attempts, counseling sessions)
- Dates interventions received if documented

*These conditions require a delay in ART initiation and are thus important in evaluating Cohort 1.

*Objective 8, TB, hypertension, and diabetes cohort:*

- All fields in the Chronic Patient Record (attached). (Note: These fields may be recorded by the sites in other formats, such as registers or patient files, if the Chronic Patient Record is not yet in use; we will extract them from whatever source documents are available.)
- Dates and results of screening tests
- Dates and results of all laboratory investigations
- Dates of all clinic visits
- Prescribed medications
- Primary purpose of all clinic visits

## **c. Duration of Follow Up**

Study enrollment will begin on the date of determination of eligibility for an intervention (Cohorts 1-5) during the enrolment period. Enrolment for cohort 8 will begin if date of eligibility (screening or diagnosis date) was in the last month for TB and Hypertension patients and within the last 6 months for Diabetes patients.

Passive follow up through medical record review will continue for a minimum of 14 months after the date of enrollment (two additional months beyond twelve months to allow one year outcomes to occur). This will allow all subjects sufficient follow up time to complete each of the primary outcomes designated. Patients enrolled early in the study will have up to 20 months of passive follow-up, assuming a six-month enrollment period. Medical records will be checked for each patient after each clinic visit.

## **d. Data Entry and Storage**

During the enrollment period, which we anticipate to last for approximately six months, patients will be identified and enrolled from TIER.Net (Cohorts 1-5) and site records (TBHD cohort) consecutively until sample size targets are met. “Enrollment” will consist only of reviewing site records to select patients who have become newly eligible for the study in the previous interval; there will be no contact with patients for study purposes.

As explained above, the study will not generate any new data beyond what is called for by existing guidelines and procedures. To allow a valid evaluation, we will make efforts to ensure that the data the clinics are supposed to record are collected and documented completely and promptly. Study staff will visit the sites regularly to obtain electronic data sets, capture paper records and registers on electronic case report forms on dedicated tablets, and review data quality. If needed, study staff will assist the sites to complete all routine forms and records and enter them into a database. Once initial data collection systems are in place, we anticipate visiting each site at least every 10 days to collect data sets, review procedures, and respond to data queries from the previous visit. In order to ensure a secure transmission, the electronic data sets obtained from the clinic will be transferred from the study site via a dedicated secure VPN onto protected drives at the local office.

We anticipate entering all data not captured electronically at the facility onto electronic case report forms on tablets on site, so that paper forms do not need to be removed from the study clinics. Once patient information is captured on the tablet, the information will be immediately sent to a highly secure cloud server and wiped from the tablet. The data will then be downloaded onto secure, protected drives at the local office and at Boston University via a dedicated secure VPN. In some cases (e.g. if there are power failures or other difficulties with using computers on site), it may be necessary to enter data onto paper study forms and then enter them into a database at the local office. These forms will be stored in a locked cabinet at the office, which is itself a secure facility, with access to all study cabinets limited to the study team. All electronic data files will be stored on secure, protected drives at the local office and at Boston University, with access limited to relevant study staff.

All subjects will be assigned a seven-digit, sequential identification number. The first three digits will identify the facility, the fourth digit will indicate the study population/cohort and the remaining three digits will be a consecutive number based on subjects as they are enrolled and will specify the individual subject. The study ID number will be used to identify individual subjects in the study databases and for all data analysis.

For each subject, a national ID number, electronic clinic record number, date of birth, and name will be collected to allow linking of fields extracted from multiple data sources (registers, records, lab reports, etc.). An electronic linking file will be created to link this information to a patient ID number. The linking file will be stored separately from all other data on secure laptops or tablet computers and will be transferred between the head office, where it will be created, and field staff only via the secure cloud server or VPN with access limited to the study team. The linking file will be kept until all data collection is complete and all data has been linked. Once the linking is complete, the linking file will be destroyed. All data collection files will be coded using patient ID numbers and not contain subject identifiers.

MSAcess or a similar software program requiring secure log-in and access by invitation will be used to create an electronic database to manage study data. The database will be managed at the HE2RO Johannesburg office by the study team. On a regular basis, the data will be converted to SAS, STATA or SPSS for cleaning and data analysis. Quality of the data will be assured by comparing a subset of values in the database to the study patient files. Additionally, data files will be reviewed by the study team on a monthly basis and queries returned to the site-level staff for response. All data management and analytic databases will be password protected with access restricted to the members of the study team. Any linking files created for data collection will be destroyed once data entry from source records has been completed and the analytic data set cleaned and closed. A fully de-identified data set will be made available through one or more open access portals when the study is closed.

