## **a. Fast Track ART Initiation Counseling**

Fast track initiation seeks to reduce attrition from chronic care by speeding up the process of treatment initiation for patients who are eligible for treatment and thereby increasing the proportion of treatment-eligible patients who start treatment promptly. For HIV, the goal is to reduce the total number of visits that patients need to complete in order to start treatment and allow patients to initiate treatment over the course of two clinic visits within one week of confirming ART eligibility, with additional counseling provided in the first two routine visits after treatment initiation. The intervention includes a detailed curriculum for the counseling sessions, and providers work with patients to create an individualized adherence plan and ensure post-initiation adherence support[12].

| *Primary outcome:* | Proportion of ART-eligible patients who initiate ART (obtain their first supply of ARV medications) within 30 days of determination of treatment eligibility |
| --- | --- |
| *Eligibility:* | All non-pregnant adult patients who are eligible for ART according to national guidelines (CD4 cell count ≤ 500 or Stage 3 or 4 condition) |
| *Sample size:* | 720 (360 per arm; 30 per cluster) |
| *Data sources:* | HIV counseling and testing (HCT) and CD4 count registers; adherence plans; Tier.Net (South Africa’s national HIV patient care database); counselling registers and other registers or records that document services received prior to ART initiation (including patient record) |

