# STUDY SITES AND POPULATION

## **a. Selection and Randomization of Study Sites**

The evaluation will be conducted at 24 primary health care clinics (PHCs) in South Africa. Six clinics will be chosen from one district each in Gauteng, KwaZulu Natal, Limpopo, and North West Provinces. These provinces have been chosen in consultation with NDOH as they are high HIV burden provinces with high burden districts and high volume clinics. Criteria for selection of clinics are:

- *High patient volume*. Although the adherence guidelines apply to multiple conditions, the impact evaluation will focus on HIV (ART initiation, retention, and adherence). To achieve adequate enrollment within the time frame of the evaluation, only sites with >1000 current ART patients will be included. (It is likely that these will be large clinics in general and thus also have relatively high volumes of TB, diabetes, and hypertension patients for Objective 8.)

- *Not already a National Health Insurance pilot site*. The NDOH is piloting a series of interventions in selected districts in preparation for the introduction of national health insurance. These districts will be excluded as they are already providing enhanced care and therefore it would be difficult to assess the impact of the minimum package interventions.
- *Generating computerized Tier.Net data*. Some clinics continue to use only paper records to record and report on ART patients. Since the evaluation will rely heavily on patient records, it will not be practical to work at sites that have not yet implemented a computer-based system. (Note that we can work at sites that are not yet networked under Tier.Net, South Africa’s national HIV patient care database, just not at those that remain paper-based.)

- *Not participating in any other adherence-related studies or pilots*. Although most clinics will already be providing some degree of adherence support to patients, under existing guidelines, a few may also be participating in research or special programmes pertaining to adherence. We would like to avoid these so that the impacts observed can be attributed to the adherence guideline interventions.

The NDOH will develop a short list of all sites in each participating province that meet these criteria. We will then assist NDOH to select three matched pairs of clinics per province. The criteria for matching are:

- *Size*. Both clinics in each pair should have either 1000-1999; 2000-4999; or ≥5000 current ART patients.

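### Cohort 1 is enrolled from TIER.Net to measure ART start, but nothing in the protocol shows that TIER.Net lists patients at eligibility, so non-starters may be missing from the denominator

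*Protocol*

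**What the plan says.** Section 9d is the only place that names the source from which patients are enrolled: "patients will be identified and enrolled from TIER.Net (Cohorts 1-5) and site records (TBHD cohort) consecutively until sample size targets are met". It sets TIER.Net, for Cohorts 1-5, against site records, for the tuberculosis, hypertension and diabetes cohort. The next sentence is looser: enrolment "will consist only of reviewing site records to select patients who have become newly eligible for the study in the previous interval".

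Section 4a gives the Cohort 1 primary outcome as "Proportion of ART-eligible patients who initiate ART (obtain their first supply of ARV medications) within 30 days of determination of treatment eligibility". Table 3 repeats it as the short-term outcome. The denominator is therefore everyone who becomes eligible.

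Section 4a also lists the Cohort 1 data sources: "HIV counseling and testing (HCT) and CD4 count registers; adherence plans; Tier.Net", followed by "counselling registers and other registers or records that document services received prior to ART initiation (including patient record". These are sources of data. The section does not say that patients are enrolled from them.

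The list of data fields in section 9b includes "Date treatment eligibility determined, if reported", so the date that defines entry to the cohort may be absent for some patients.

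**The concern.** A cohort whose outcome is starting treatment needs a list that is fixed before treatment starts. If a patient's chance of being on the list depends on having started, the list depends on the outcome. Cohorts 2-5 do not share this problem, because their inclusion criteria (section 8b) require patients to have started ART already.

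No section says that an eligible patient is entered in TIER.Net before the first ARV supply, and none compares the TIER.Net list with the testing and CD4 registers. The site-visit and data-quality procedures in sections 9a and 9d aim at complete records and complete electronic entry. They do not state a search for eligible patients who are absent from the list.

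At stake are the two initiation proportions, the relative risk between arms and possibly its direction. An analysis plan written later cannot recover patients who were never enrolled.

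**Working it through.** **Inputs from the protocol.** Initiation of 60% without and 75% with the intervention (Table 4); 24 clinics, 12 per arm; coefficient of variation 0.1, power 80%, alpha 0.05 (section 10b; two-sided assumed); 30 patients per clinic, 720 in total, after a 20% increase for ineligible patients (Table 4).

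**Input not in the protocol.** f, the share of eligible patients not started by 30 days who are missing from the enrolment list. It is an assumption and could lie anywhere from 0 to 1.

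**Step 1: reproduce the plan's figure.** Use the Hayes-Bennett formula solved for cluster size m, with 12 clusters per arm, t quantiles on 11 degrees of freedom (12 pairs) and k = 0.1:

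m = [p0(1−p0) + p1(1−p1)] / [(12−1)(p1−p0)²/F − k²(p0² + p1²)]

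- F = (2.201 + 0.876)² = 9.465
- m = (0.24 + 0.1875) / [11 × 0.0225/9.465 − 0.01 × (0.36 + 0.5625)] = 25.3
- 25 × 1.2 = 30 per clinic, and 30 × 24 = 720

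The stated sample size reproduces, and this point does not dispute it. The 20% increase is for ineligible patients and cannot correct a selective list.

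**Step 2: observed proportions with equal loss in both arms.** Observed rate = p / [1 − (1−p)f].

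- f = 25%: 0.60/0.90 = 66.7%; 0.75/0.9375 = 80.0%
- f = 50%: 0.60/0.80 = 75.0%; 0.75/0.875 = 85.7%
- f = 75%: 0.60/0.70 = 85.7%; 0.75/0.8125 = 92.3%

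**Step 3: power.** Use a cluster-level t test with 22 degrees of freedom and 25 evaluable patients per clinic (30/1.2). The planned between-clinic SDs are 0.1 × 0.60 = 0.060 and 0.1 × 0.75 = 0.075. Missing non-starters push rates towards 1 and so compress these SDs as well. Each is multiplied by the derivative of the step 2 formula, (1−f)/[1 − (1−p)f]². At f = 75% this gives 0.060 × 0.25/0.70² = 0.031 and 0.075 × 0.25/0.8125² = 0.028.

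Variance per pair of clinics = [q0(1−q0) + q1(1−q1)]/25 + SD0² + SD1², where q is the observed rate. The noncentrality is (q1−q0)/√(variance/12).

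| f | Observed rates | Difference (points) | Relative risk | Noncentrality | Power |
|---|---|---|---|---|---|
| 0 | 60.0% v 75.0% | 15.0 | 1.25 | 3.20 | 86% |
| 25% | 66.7% v 80.0% | 13.3 | 1.20 | 3.08 | 84% |
| 50% | 75.0% v 85.7% | 10.7 | 1.14 | 2.85 | 78% |
| 75% | 85.7% v 92.3% | 6.6 | 1.08 | 2.35 | 61% |

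**Step 4: loss in one arm only.**

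- Comparison arm only: the difference is 75.0 − 66.7 = 8.3 points at f = 25%, and 75.0 − 75.0 = 0 at f = 50%.
- Intervention arm only: 80.0 − 60.0 = 20.0 points at f = 25%, and 85.7 − 60.0 = 25.7 at f = 50%.
- No true effect (60% in both arms), loss in the intervention arm only: a spurious 6.7 points at f = 25% and 15.0 at f = 50%.

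Unequal capture is possible. Section 4 adds an enrolment route at intervention sites only, for eligible patients who receive the intervention.

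**The case against.** The strongest reply is that the harmful premise is not in the document. Section 4a describes Tier.Net as the national HIV patient care database and names it among the Cohort 1 sources. The sentence in section 8a, "Some clinics continue to use only paper records to record and report on ART patients", might lead a reader to infer that TIER.Net holds only patients on ART. It describes paper-based clinics that are not selected, and it does not say what TIER.Net contains. That inference is not supported, and f may be zero.

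A reader might also infer that sections 4a and 9d flatly contradict each other. They do not: patients can be identified in one system and their data drawn from several, and the looser sentence in section 9d leaves room for register review. The two sections are unreconciled, which is a lesser fault.

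Two further limits stand. The calculation applies f to everyone not started by 30 days. Some of them start later and might then appear on the list, so high values of f are less plausible than low ones. It is also tempting to hold the coefficient of variation at 0.1 on the inflated rates, which gives power of 78%, 61% and 30%. That ignores the compression of between-clinic variation produced by the same mechanism, and it overstates the loss.

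What the reply does not remove is that the only stated enrolment source is one whose coverage at eligibility is never established or checked. The efforts towards complete electronic entry and the visits at least every 10 days reduce the risk. They are not a comparison of the list with the registers.

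**Conclusion.** The point holds as a gap in the enrolment rule. Section 9d ties Cohort 1 to a list that may depend on the outcome, and the protocol offers nothing to show that it does not. It does not establish that patients are in fact missing.

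With equal loss, the effect on power is modest up to f = 50%, where power is still about 78%. The distortion of the proportions is larger: the comparison-arm rate moves from 60% to 75% at that value, and the difference shrinks from 15.0 to 10.7 points. A reader might infer that the bias always runs towards no effect. That is true only for similar loss in both arms. If loss differs by arm, the planned effect can disappear or a spurious one can arise.

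All of these sizes rest on the assumed f, on the planned 60% and 75%, and on the planned between-clinic SDs. The sample size is not in question.

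**What to change.** In section 9d, separate Cohort 1 from Cohorts 2-5. Enrol Cohort 1 consecutively by the date eligibility was determined, by the same procedure in both arms. Use the combined pre-ART sources already listed in section 4a (testing and CD4 registers, counselling and other pre-ART registers, patient records) together with TIER.Net. The testing and CD4 registers alone would not be enough, because section 8b also admits patients on WHO stage, TB or cryptococcal meningitis.

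Reconcile the TIER.Net list against those registers at every clinic. Then use TIER.Net, clinic files and laboratory records to follow enrolled patients for ART start and viral load. Keep TIER.Net as the enrolment source for Cohorts 2-5.

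The cost is a change of wording and somewhat more register capture for one cohort of about 30 patients per clinic. The registers are already named as sources, capture of paper registers is already planned, and staff already expect to visit each site at least every 10 days.

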# DATA ANALYSIS

## **a. Outcomes**

Table 3 lists the primary and secondary outcomes we will measure for each of the objectives. Each primary outcome includes both a short term (S) outcome and a longer term (L) outcome for assessment of the immediate and longer term outcomes of the intervention. Our ability to assess secondary outcomes will depend on data availability and duration of follow up. Note that viral suppression in the current South African ART guidelines is defined as viral load below 400 copies/ml^3^, and this is the threshold that the National Health Laboratory Service will report, and is therefore what we will use.

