## **d. Enhanced Adherence Counseling**

The goal of this intervention is to identify patients who have poor treatment adherence as indicated by an elevated viral load and target these patients for enhanced adherence counseling to help them improve their adherence. Although HIV-infected patients with detectable viral loads may receive additional adherence counseling under standard of care, this intervention will standardize and intensify that counseling. The intervention includes one or two structured education/counseling sessions in which effective strategies for achieving good adherence are discussed and goals set for viral re-suppression.

| *Primary outcome:* | Proportion of patients with an elevated viral load who are alive, in care and resuppress their viral load within 3 months of eligibility for enhanced adherence counseling |
| --- | --- |
| *Eligibility:* | All adult patients with a detectable viral load at a routine monitoring visit |
| *Sample size:* | 1008 (504 per arm; 42 per cluster) |
| *Data sources:* | NHLS laboratory database; Tier.Net; adherence plans; counselling registers or other registers or records that document provision of counselling |

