## **b. Sample Size**

Table 4 shows the sample size that is required to detect meaningful differences for Objectives 1-5 and for estimating precise rates for Objective 8. Each sample size is determined to measure our short term outcome for the objective. For Objectives 1-5, all calculations assume a site-clustered design with the clinic as the cluster; 24 clusters evenly split (randomized) between intervention and comparison groups; a coefficient of variation of 0.1, 80% power; and an alpha of 0.05.

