## **c. Data Analysis Objectives 1-5**

Our general analytic plan will be the same for each of Cohorts 1-5. We will begin with descriptive analyses of the characteristics of each of the cohorts stratified by intervention/non-intervention (comparison) cohorts. We will also look for differences within the randomized matched pairs. Because the data will be collected as part of a clustered design, the data analysis will need to account for clustering. For each primary outcome described above, we will conduct a crude analysis comparing the proportion of subjects with the outcome in the intervention and comparison arms. Next we will conduct an analysis for each outcome accounting only for clustering using generalized estimating equations (GEE) with an unstructured correlation matrix and clustering by treatment site. In all cases the outcomes are dichotomous and therefore we will calculate relative risks comparing the intervention to the comparison arms using a log link function and a binomial distribution. Next, should any imbalances between treatment groups be detected, we will adjust for those covariates in our GEE model. Finally, we will look for differences in the effects of the strategies by important baseline characteristics (e.g. size of the treatment population, rural vs. urban, province, etc.) using stratified analyses.

We note that because each of the interventions is targeted at a different population with the exception of decentralized medication delivery and adherence clubs, which would not be delivered to the same people at the same time, we can estimate the impact of each intervention separately, as only one of them will be delivered to each cohort within a clinic at any one time. Since some patients may participate in more than one intervention (e.g. fast track initiation followed by tracing), we will conduct a sub-analysis restricted to those who received only one intervention to look for the effects of each intervention by itself.

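### The protocol contradicts itself on the primary outcome of Objectives 1-5: section 4 and the sample size use the short-term outcome alone, section 10a and Table 3 make the long-term outcome primary as well

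*Protocol*

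**What the plan says.** Section 4 describes the five interventions, each with a box that has one primary-outcome entry. In every box that entry is the short-term outcome only. For fast track counselling (4a) it is "Proportion of ART-eligible patients who initiate ART (obtain their first supply of ARV medications) within 30 days of determination of treatment eligibility". For enhanced adherence counselling (4d) the entry counts those "who are alive, in care and resuppress their viral load within 3 months of eligibility for enhanced adherence counseling". The boxes in 4b, 4c and 4e follow the same pattern.

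Section 10a reads differently: "Each primary outcome includes both a short term (S) outcome and a longer term (L) outcome". Table 3 carries this out, with an S and an L outcome in the primary column for each of Objectives 1-5. In the Objective 6 row of the same table, the short-term outcomes are in the primary column and the long-term ones in the secondary column, although the text there still calls the latter primary.

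Section 10b says: "Each sample size is determined to measure our short term outcome for the objective". The inputs are "24 clusters evenly split (randomized) between intervention and comparison groups" and "a coefficient of variation of 0.1, 80% power; and an alpha of 0.05". This is the only alpha given for Objectives 1-5.

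Section 10c begins its comparative analysis with: "For each primary outcome described above, we will conduct a crude analysis". Clustered and adjusted relative risks follow. It makes no distinction between S and L.

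**The concern.** Naming the primary outcome is a matter for the protocol, and here it is done in two incompatible ways. An SAP that adopted either reading would still contradict one part of the protocol.

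The choice affects the conclusion. In Objectives 1-3 the two outcomes are different endpoints: starting ART or collecting medication on the one hand, viral suppression on the other. They can disagree. An intervention could bring forward ART initiation without improving suppression at nine months, or the reverse. As the text stands, either result could be reported as a positive primary finding, in an evaluation meant to inform a national rollout.

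Two other parts of the protocol depend on the same definition. Section 10e and the Objective 7 row of Table 3 cost each intervention per primary outcome achieved, in the singular, so the denominator is ambiguous. Section 10b promises to raise the sample size if analytic power is inadequate, without saying for which outcome.

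**Working it through.** **1. The statements side by side**

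| Place in the protocol | Short-term outcome | Long-term outcome |
|---|---|---|
| Section 4a-4e boxes | Primary | Not listed |
| Section 10a text; Table 3, Objectives 1-5 | Primary | Primary |
| Table 3, Objective 6 row | Primary column | Secondary column, but called primary |
| Section 10b | Basis of the sample size | Not sized |
| Section 10c | Analysed as a primary outcome | Analysed in the same way |

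Section 9c also sets the minimum follow-up at 14 months so that one-year outcomes can occur and the primary outcomes can be completed. Primary status for L in section 10a is therefore unlikely to be a slip.

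**2. Does the sample size rest on S at a single 0.05?**

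Inputs from section 10b and Table 4: 12 clinics per arm, coefficient of variation k = 0.1, 80% power, alpha 0.05 (two-sided assumed), 20% inflation. Objective 1 assumes 60% versus 75%. The formula is the Hayes-Bennett one for matched clusters, with t quantiles on 22 degrees of freedom:

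m = f[p0(1−p0) + p1(1−p1)] / {(c−2)(p1−p0)² − f·k²(p0² + p1²)}, with f = (2.074 + 0.858)² = 8.60.

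- Numerator: 8.60 × (0.24 + 0.1875) = 3.675.
- Denominator: 10 × 0.0225 − 8.60 × 0.01 × 0.9225 = 0.225 − 0.0793 = 0.1457.
- m = 25.2 per clinic; 25.2 × 1.2 × 24 ≈ 727, against the stated 720.

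The same formula gives 19.3 per clinic for Objectives 2 and 3 (80% versus 95%) and 19.7 for Objective 5 (30% versus 45%). Each rounds up to 20, and 20 × 1.2 × 24 = 576, as stated. Objective 4 (52% versus 67%) gives 24.8, rounded up to 25, hence 720 against the stated 1,008. That figure is not reproduced; it exceeds what the formula needs and does not bear on this point. Apart from Objective 4, the planned sizes agree with one test of S at 0.05 with no split.

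**3. Error rate if either outcome could count**

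Assumption, not in the protocol: S and L are each tested at two-sided 0.05, and success on either is a positive primary result. If the tests are independent, the rate is 1 − 0.95² = 0.0975. For test statistics with correlation r, it is 1 − P(|Z1| < 1.96 and |Z2| < 1.96) under a bivariate normal:

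| r | Rate | Multiple of 0.05 |
|---|---|---|
| 0 | 0.0975 | 1.95 |
| 0.3 | 0.095 | 1.9 |
| 0.5 | 0.091 | 1.8 |
| 0.7 | 0.084 | 1.7 |
| 0.8 | 0.078 | 1.6 |
| 0.9 | 0.070 | 1.4 |

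The protocol gives no correlations. In Objective 5, return by three months implies return by twelve, so the patient-level correlation is √[p(1−q)/(q(1−p))], where p is the three-month and q the twelve-month proportion. Assuming p = 0.30, it is √(0.18/0.28) = 0.80 at q = 0.40 and √(0.12/0.42) = 0.53 at q = 0.60. If the test statistics are correlated to about the same degree, the rate is about 0.08 to 0.09. In Objective 4, S and L are the same endpoint at two times, so a high correlation is plausible there too.

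**4. Two ways to hold 0.05 per intervention**

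- *Split alpha, 0.025 each.* With the same formula and inflation, 80% power for S needs about 1,035 patients (Objective 1), 1,049 (each of Objectives 2 and 3), 973 (Objective 4, within the planned 1,008) and 724 (Objective 5). With the full planned numbers, power for S is about 75%, 74%, 86% and 78% in the same order.
- *Fixed sequence, S then L.* If S has no effect, any claim first needs a false positive on S, with probability at most 0.05. If S has an effect and L does not, a false claim on L has probability at most 0.05. Sample size and power for S do not change.

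**The case against.** The strongest reply is that this is an SAP matter. Testing order and division of alpha commonly sit in the SAP, which is not at hand, so their absence from the protocol is not a fault. That stands, and the point does not rest on it.

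A reader might go further and infer that the plan tests both outcomes at the full 0.05 with no hierarchy, so that the false-positive rate per intervention is nearly double the stated alpha. The document does not support this. The 0.05 appears only as an input to a sample size for S. Section 10c sets no significance level and no rule for declaring an intervention effective. The section 4 boxes, the sizing and the Objective 6 columns all lean towards S, and if S alone is primary the rate is 0.05. Nearly double also needs near-independence.

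A reader might likewise count ten primary tests across the five objectives. The protocol presents the interventions as addressed to different patient groups and evaluated separately, and it makes no claim that at least one of them works. A package-wide error rate is therefore not at issue.

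Section 4 also says that further detail on outcomes comes later, so its single entries could be abbreviations. This softens the conflict without removing it. The boxes do not mark their entry as one of two, and the Objective 6 row still contradicts its own label. Finally, sizing on S alone is openly stated and is no fault in itself.

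**Conclusion.** The point holds as an internal contradiction over whether the long-term outcome is primary in Objectives 1-5. It needs no assumption about the SAP, because both statements stand in the protocol.

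The statistical consequence is conditional. If either outcome at two-sided 0.05 counted as a positive primary result, the false-positive rate per intervention would be about 0.07 to 0.0975, or 1.4 to 1.95 times 0.05, for correlations from 0.9 down to 0. The lower part of the range is more plausible for Objectives 4 and 5, where the outcomes are repeated or nested. The success rule, the two-sided test and the correlations are assumptions. The protocol should be corrected, and the correction is a matter of wording.

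**What to change.** In section 10a and Table 3, name the short-term outcome as the single primary outcome of each of Objectives 1-5, in line with section 4 and the sample size. Make the long-term outcome the key secondary, and remove the word primary from the long-term entry in the Objective 6 row. In section 10c, state that the long-term outcome is tested at 0.05 only if the short-term outcome is significant, and is otherwise reported as an estimate with a 95% confidence interval. State also that the five objectives are separate questions. The cost per primary outcome in section 10e then has one meaning.

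This needs no extra patients or data and leaves power for the short-term outcome as planned. The cost is that a long-term benefit, such as better viral suppression, could not be claimed as confirmatory where the short-term test fails. If the investigators want a confirmatory long-term claim regardless of the short-term result, splitting alpha is the alternative, at the price in patients or power shown above.
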